### Recruitment Methods

Medical student participants will be recruited via the Medical Protection Society (emails to medical student members), the Medical Schools Council (email cascade to UK medical schools), direct email communications to heads of UK medical school and via posts on social media (LinkedIn, BlueSky, Twitter, Instagram). Participants will then be directed to a Qualtrics survey online where they will have access to the participant information sheet before being asked to complete the online consent form and baseline measures.

For the process evaluation, medical educators in schools with participating students who were allocated to the intervention arm will be contacted via emails sent to heads of medical schools with participating students. Trial therapists will be contacted directly via email.

Regarding the recruitment period, the recruitment of medical students commenced on 16^th^ June 2025 and is expected to end on the 31^st^ March 2026. Following this, the recruitment of Medical Educators and trial therapists for the process evaluation is scheduled to commence July 2026 and is expected to be completed by no later than October 2026.

### Intervention

#### Participants randomised to THUMOS (Experimental group).

Thumos is a brief, manualised cognitive-behavioural coaching programme developed specifically for medical students, involving case studies of stressful events medical students may experience on placements. It is based upon the principles of the Reboot (Recovery-boosting) coaching programme, an earlier CBT-based resilience intervention for healthcare professionals and trainees [9,22–26]. Thumos is preventative in focus, equipping students with cognitive and behavioural strategies before, rather than only in response to, the stressful events intrinsic to clinical training. It is grounded in cognitive-behavioural therapy (CBT), in which thoughts, emotions, physical sensations and behaviours are understood as interconnected, such that modifying unhelpful thinking and behaviour can improve emotional wellbeing [28,29]. It also draws on resilience theory [30]. The strategies taught are cognitive (for example, challenging negative automatic thoughts and reattributing responsibility), behavioural (for example, mood-boosting activities, problem-solving and breathing exercises) and meta-cognitive (worry postponement and gratitude). The full intervention manual is available from the authors on request.

The programme runs over four weeks and comprises two online group workshops (120 minutes each, in stable groups typically of around four to eight) and one individual coaching call (60 minutes), with an intervening practice week. All sessions are delivered remotely by qualified therapists (HCPC-registered Clinical Psychologists or BABCP-accredited CBT therapists) trained in the Thumos protocol, and participants receive a workbook in advance.

**Workshop 1** addresses the CBT model, identifying and challenging negative automatic thoughts, common unhelpful thinking habits (for example, catastrophising and mind-reading), and the role of beliefs and self-esteem. Individual exercises include mapping a personal placement stressor onto the CBT model (identifying the most distressing “hot thought”) and completing a thought record. Group-based activities include a facilitator-led formulation of a shared example and discussion of a medical-student case study to spot thinking habits.

**Workshop 2** addresses the physiological stress response and breathing exercises, mood-boosting activities, reducing self-blame through balanced appraisals of responsibility, and a five-step problem-solving activity. Individual exercises include a guided breathing exercise, a personal mood-boosting plan, and a “responsibility pie chart”. Group-based, breakout-room activities use medical-student case studies to distinguish helpful from unhelpful behaviours and to practise responsibility appraisal and problem-solving.

**The individual coaching call** personalises the content: the facilitator reviews the strategies tried, identifies “stuck points”, and chooses from a selection of CBT-based intervention strategies (e.g., self-statements and thought challenging, gratitude, distraction, postponing worry, breathing exercises) using a decision tree, before co-producing a personal “blueprint” of takeaways and support sources.

To ensure the quality and fidelity of the Thumos intervention throughout the trial, a structured fidelity monitoring protocol is in place whereby researchers observe a minimum of 20% of workshop cycles and review recordings of 10% of individual video/phone calls, using documented fidelity assessment criteria. Therapists complete workshop diaries capturing their experiences of intervention delivery, including perceived benefits and challenges, and researcher field notes track any deviations from the protocol in real time. Participant adherence is defined as completion of both group workshops with at least 75% attendance at each session, and those who miss sessions are proactively contacted by email, text, and telephone to support engagement. The quality of qualitative process data is further strengthened through credibility strategies including respondent validation of transcripts, peer debriefing, and negative case analysis.

### Participants Randomised to Control Group

Control condition participants will not receive an alternative intervention. However, they can continue to access mental health services that are usually available via medical schools, universities or to the public throughout the period that they are participating. A flow diagram of the participants journey through the trial can be seen in Fig 2.

**Fig 2 pone.0355371.g002:**
[figure not shown]
Flow diagram of participants through the trial.

### Data Collection and Outcome Measures

A core online questionnaire set including measures of resilience (Brief Resilience Scale [31]), burnout (Oldenburg Burnout Inventory; OLBI [4]) confidence in coping with adverse events (CCAE [9]) depression (Patient Health Questionnaire, PHQ-9 [32]), mental health (Recovering Quality of Life-Utility Index, ReQoL-UI [33]) sickness absence and support access will be completed at T1, T2, T3 and T4 (see Tables 1 and 2). In addition, at T2 a process questionnaire will be added to this dataset (see Table 3).

**Table 1 pone.0355371.t001:** Outcome measures.

Outcome	Time	Variable definition	Effect measure
BRS (primary)	T3	BRS mean score	Adjusted mean difference/Cohen’s *d*
BRS (secondary)	T4	BRS mean score	Adjusted mean difference/Cohen’s *d*
CCAE	T3/T4	CCAE mean score	As above
OLBI	T3/T4	OLBI total and subscales	As above
PHQ-9	T3/T4	PHQ-9 total score	As above
ReQoL-UI	T3/T4	Utility score	As above
ReQoL-UI QALYs	BL-T4	QALYs area under the curve	Adjusted mean difference
Sickness absence	T3/T4	Days lost in past 4 weeks	Adjusted rate ratios with 95% CI

BRS: Brief Resilience Scale; CCAE: Confidence in Coping with Adverse Events; OLBI: Oldenburg Burnout Inventory; PHQ-9: Patient Health Questionnaire-9 item depression scale; ReQoL-UI: Recovering Quality of Life – Utility Index; QALYs: Quality-adjusted life years; BL: Baseline; T1, T2, T3, T4: Time points 1, 2, 3, and 4 (T = time)

**Table 2 pone.0355371.t002:** Outcome scoring.

Outcome	Items	Measure	Construct(s) & direction	Time points	Derived variable/scoring (incl. item response scale)
BRS (Primary)	6	Brief Resilience Scale	Resilience; higher = better	T3 [12–24 wks]	Mean of the six items after reverse scoring items 2, 4 and 6. Each item rated on a 5-point scale: 1 (Strongly disagree), 2 (Disagree), 3 (Neutral), 4 (Agree), 5 (Strongly agree).
BRS	6	Brief Resilience Scale	Resilience; higher = better	T4 [30–44 wks]	Mean of the six items after reverse scoring items 2, 4 and 6; each item rated 1 (Strongly disagree) to 5 (Strongly agree), with a “Neutral” midpoint.
CCAE	3	Confidence in Coping with Adverse Events questionnaire	Confidence coping with adverse events; higher = better	T3, T4 [12 –24, 30–44]	Mean of 3 items. Each item rated on a 4-point scale: “No – not at all”, “Unsure”, “Yes – to some extent”, “Yes – definitely”.
OLBI (total & subscales)	16	Oldenburg Burnout Inventory	Burnout (exhaustion, disengagement); higher = worse	T3, T4 [12 –24, 30–44]	Subscale means and total mean, with reverse scoring of positively worded items according to the published scoring instructions. Each item rated on a 4-point scale: Strongly disagree, Disagree, Agree, Strongly agree.
PHQ-9	9	Patient Health Questionnaire-9	Depressive symptoms; higher = worse	T3, T4 [12 –24, 30–44]	Total score obtained by summing the nine items (range 0–27). Each item rated over the past two weeks: 0 (Not at all), 1 (Several days), 2 (More than half the days), 3 (Nearly every day).
ReQoL-UI (utility)	10	Recovering Quality of Life – Utility Index (ReQoL-UI)	Quality of life utility; higher = better	T3, T4 [12 –24, 30–44]	Utility index derived via the published ReQoL-UI algorithm, which combines the 10 mental-health items with the single physical-health item. Each mental-health item is rated on a 5-point scale from “None of the time” to “Most or all of the time” and coded 0–4 before the algorithm is applied; the physical-health item is rated from “No problems” to “Severe problems”.
ReQoL-UI QALYs	10	Recovering Quality of Life – Utility Index (ReQoL-UI)	Quality adjusted life years; higher = better	Baseline–T4	Area under the utility-time curve (derived from the utility scores above; no separate item response scale).
Sickness absence	2	Sickness absence items	Days lost last 4 weeks; higher = worse	T3, T4 [12 –24, 30–44]	Count of days lost in past 4 weeks (free numeric response).

BRS: Brief Resilience Scale; CCAE: Confidence in Coping with Adverse Events; OLBI: Oldenburg Burnout Inventory; PHQ-9: Patient Health Questionnaire-9 item depression scale; ReQoL-UI: Recovering Quality of Life – Utility Index; QALYs: Quality-adjusted life years; T3, T4: follow-up time points.

**Table 3 pone.0355371.t003:** Questionnaire assessment schedule.

	Baseline	T2 (post intervention or equivalent time)	T3 (4 month follow up)	T4 (9 month follow up)
**Enrolment**				
Informed consent form	X	–	–	–
**Primary outcome**				
Brief Resilience Scale (BRS)	X	X	X	X
**Secondary outcomes**				
Oldenburg Burnout Inventory (OLBI	X	X	X	X
Confidence in coping with Adverse Events (CCAE) questionnaire	X	X	X	X
Patient-Health Questionnaire-9 (PHQ-9)	X	X	X	X
Recovering Quality of Life-Utility Index (ReQoL-UI)	X	X	X	X
Self-reported sickness absence	X	X	X	X
Other measures (descriptive only)				
Support access	X	X	X	X
**Process evaluation**				
Process questionnaires	–	X	–	–

#### Primary outcome.

**To determine whether Thumos is superior to SAU at a 4-month follow-up in increasing psychological resilience.**

Brief Resilience Scale (BRS): The 6-item BRS measures perceptions of personal resilience, including ‘I tend to bounce back quickly after hard times’. This questionnaire has good internal reliability (α = .80−.91), concurrent validity with other resilience questionnaires [31], and detects learning changes [9].

#### Secondary outcomes.

**To determine whether Thumos is superior to SAU at 4-month and 9-month follow-ups in the endpoints of confidence, burnout, depression, mental health, and self-reported sickness absence.**

Oldenburg Burnout Inventory (OLBI). The scale comprises 16 items and two subscales (exhaustion and disengagement). It has been used widely and found to have good internal reliability (α = .88) [4].Confidence in coping with Adverse Events (CCAE) questionnaire: This 3-item questionnaire assesses how confident participants are in coping with adverse events, e.g., ‘If I was involved in an adverse event for which I thought I held some responsibility I know the things I would do to help manage my stress levels’. Previous studies suggest this scale has good internal reliability (α = 0.85) [26] and detects learning changes [9].Patient-Health Questionnaire-9 (PHQ-9). This 9-item questionnaire is widely used to measure depression and has been validated in various groups, including medical students [34]. It has good internal consistency (α = .83) and captures fluctuations [35].Recovering Quality of Life-Utility Index (ReQoL-UI) [33]. Mental health will be measured with the 10-item ReQoL-UI. This validated, reliable questionnaire measures mental health across areas of quality of life. It applies to the full spectrum of mental health conditions and provides Quality of Life Adjusted Years (QALY) estimates.Self-reported sickness absence. Two items will be used to measure sickness absence, the first which asks about total days lost within the past 4 weeks; the second of which asks how many working or studying days specifically were lost within this timeframe.

Other Measures:

Support access. Four items will be used to assess whether participants are accessing any form of psychological wellbeing service, which type of support they are accessing, when they began accessing this, and when they anticipate, they will stop accessing this. These data will be collected at baseline, T2, T3 and T4 and summarised descriptively by arm and time point to describe support received alongside trial participation. Support access is not a secondary efficacy outcome and will not be analysed using models or used as a covariate.

### Process evaluation outcomes

**To assess acceptability and how Thumos is delivered in practice through a process evaluation with users, medical educators, and providers.**

We drew upon UK Medical Research Council (MRC) guidance for process evaluations of complex interventions [36] to design a mixed-methods approach to the process evaluation.

Psychological therapist logs: Weekly logs will assess therapists’ experiences of intervention delivery, including perceived benefits, mechanisms, and challenges.Process questionnaires: Process questionnaires at T2 (post-intervention) will explore participants’ reasons for participating, and their perceptions and experiences [37]. Participants in the intervention arm will be asked about their affective attitudes to the intervention, general acceptability, perceived effectiveness, ethicality, intervention coherence and mechanisms, self-efficacy, burdens, opportunity costs, and barriers and facilitators. Participants in the control arm will be asked about their reasons for participating, and their perceptions and experiences of the study.Field notes: Researchers’ field notes will track any changes in the delivery of the intervention; enabling recording of protocol changes.Participant interviews: At T3, a randomly selected subset of participants from the intervention arm will be invited to 30-minute semi-structured interviews (n = 20) to generate information regarding intervention delivery, feasibility and acceptance, and barriers and facilitators to participation.Medical educator interviews: Once all experimental participants have completed T2 data collection, medical educators (n = 15) at schools where students have participated in the study will be interviewed to explore 1) their perceptions of the research process, and 2) perceived benefits or drawbacks of Thumos at an organisational level, 3) ways Thumos could be implemented at scale for medical students.Therapist interviews: Once all experimental participants have completed T2 data collection, all trial therapists will be invited to 30-minute semi-structured interviews exploring their experiences of delivering the intervention.

### Safety Reporting

In this study, an adverse event (AE) will be considered any untoward medical occurrence occurring in an ACTIVATE participant whether or not related to the research procedures or intervention. An adverse reaction (AR) will be defined as an untoward and unintended response in a participant that is potentially connected to any aspect of ACTIVATE. A Serious adverse event (SAE) is defined as any adverse event that is serious and is life‑threatening or may lead to death, hospitalisation, disability, or other major medical events. A serious adverse reaction (SAR) is defined as a serious adverse event (SAE) that is related to the study. Adverse events will be recorded and reviewed by the CI, and summary reports provided to the Trial Steering committee (TSC) for review of any possible patterns.

AEs will be monitored and recorded at T2 via the inclusion of a survey question. We will also monitor them via items on the process questionnaires relating to moral and ethical concerns about the study, affective attitude towards the study (like/dislike) and experience of the study (degree of comfort experienced). All participants who indicate they may have experienced an adverse event via the survey question or report significant moral or ethical concerns, strongly disliking the study or feeling very uncomfortable will be contacted for further information and to determine whether the incident can be classed as an AE, AR, SAE or SAR.

If participants indicate during any other part of the study (e.g., during the workshops, the one-to-one call, interviews, or by contacting the study team) that an AE or SAE has occurred, they will similarly be contacted by the study team and asked to provide more information.

An SAE occurring to a research participant will be reported to the Chair of the Ethics Committee where in the opinion of the Chair of TSC that the event was: i) related, that is resulted from the administration of any of the research procedures and ii) unexpected – that is, the type of event is not listed in the protocol as an expected occurrence. The CI and the trial management team will review all SAEs, whether or not they are judged to be attributable to the trial or interventions. Based on this information, and in consultation with the Chair of the TSC, they will determine whether the participant should be withdrawn, and/or the trial should be suspended, stopped or continued. All AEs, ARs, SAEs and SARs will be fully documented and included in both the final trial report and published journal article.

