## Materials and Methods

### Trial design

This study is a randomised controlled parallel groups intervention trial (see S1 CONSORT Checklist in S1 File). All United Kingdom (UK) medical schools will be invited to participate (see S3 Appendix 1 in S3 File). Participants will be self-selecting and screened for eligibility based on the criteria that they are a) UK medical student and b) in a year of study that contains a placement of one week or longer. The trial will compare Thumos to a control condition of services as usual (SAU), where medical students in either condition can continue to access available mental health support as they usually would. Data collection will occur at four time-points, Time 1 (T1), pre-intervention (baseline); Time 2 (T2), post-intervention (following completion of Thumos/6 weeks after baseline for control group); Time 3 (T3), 4 months following baseline and Time 4 (T4), 9 month following baseline (see Fig 1). All elements will be conducted online, with questionnaires administered via Qualtrics and interviews/intervention sessions via online video platform. Participants will be contacted to complete the post-baseline measures via Qualtrics using email as the first point of contact and subsequent attempts to contact will be via SMS or email. All participants that complete post-baseline measures will be awarded a £10 shopping voucher per survey as compensation. Informed consent will also be taken online, with participants asked to read the information sheet and provide written informed consent via Qualtrics prior to responding to any data collection items (see S4 Appendix 2 in S4 File). A process evaluation will include medical student participants, medical educators from medical schools of participating students and the Thumos therapists.

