### Study population for process evaluation

#### Inclusion criteria.

Participating medical students: We will recruit medical students in the main trial to also take part in the process evaluation. Both control and intervention arm students will be invited to complete process questionnaires; only intervention arm medical students will be invited to take part in qualitative interviews.

UK medical educators: We will recruit medical educators in schools with participating students within the intervention arm to qualitative interviews as part of the process evaluation.

The cognitive behavioural therapists/clinical psychologists delivering the intervention will be invited to qualitative interviews as part of the process evaluation.

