Support access will be described by arm and time, not treated as an outcome or covariate. Therapy group and therapist clustering will not be modelled. Secondary and exploratory findings will be supportive, not confirmatory. We will report unadjusted and Benjamini-Hochberg false discovery rate adjusted *p* values within separate T3 and T4 secondary outcome families [38], including BRS only at T4.

Mixed models will use available outcomes, assuming data are missing at random (MAR) given observed outcomes and covariates. We will summarise missingness patterns, response rates and stated reasons for non-response, and assess predictors using logistic regression.

Sensitivity analyses will include multiple imputation under MAR, pooled using Rubin’s rules; pattern mixture adjustments subtracting 0.10, 0.20 or 0.30 points from imputed T3/T4 BRS values in Thumos only; and carrying forward the latest observed value, using baseline if no follow-up value exists. Per protocol analyses will exclude major protocol deviations and non-adherent Thumos participants and require valid T3 BRS within 12–24 weeks of baseline.

A supplementary complier average causal effect analysis of T3 BRS will use a single instrumental variables model fitted by two-stage least squares, with allocation as the instrument for minimum adherence. Both stages will adjust for baseline BRS, age, gender and medical school. All randomised participants will be included, using multiple imputation for missing outcomes. We will report the effect and 95% confidence interval, Thumos adherence proportion and first-stage partial *F* statistic.

Residual and influence diagnostics will check model assumptions. Severe non-normality or unequal residual variances will prompt sensitivity analysis using robust standard errors clustered by participant. Robustness will be judged by consistency in the T3 effect’s direction and magnitude. Scale reliability will be reported as Cronbach’s alpha and McDonald’s omega with 95% bootstrap confidence intervals. Adverse and serious adverse events will be summarised by arm, with risk differences and 95% confidence intervals but no hypothesis tests.

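### Adverse events are asked about systematically only at T2, and further detection routes exist only in Thumos, yet by-arm risk differences are planned without a common source or window

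*Protocol article*

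**What the plan says.** Under Safety Reporting, the direct enquiry is a single item: "AEs will be monitored and recorded at T2 via the inclusion of a survey question". A second route follows: "We will also monitor them via items on the process questionnaires relating to moral and ethical concerns about the study", together with items on liking the study and on comfort. Data Collection and Outcome Measures places that questionnaire at T2 ("In addition, at T2 a process questionnaire will be added to this dataset"), and Table 3 marks it at T2 only. No AE question is described at T3 or T4, although both arms complete surveys then.

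Safety Reporting also acts on events that come up elsewhere, for example "during the workshops, the one-to-one call, interviews, or by contacting the study team". The control arm receives no alternative intervention, so it has no workshops or call. For the interviews, "only intervention arm medical students will be invited to take part in qualitative interviews".

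Trial design times T2 as "post-intervention (following completion of Thumos/6 weeks after baseline for control group". Process evaluation outcomes describes the questionnaire content separately by arm. For Thumos: "Participants in the intervention arm will be asked about their affective attitudes to the intervention, general acceptability, perceived effectiveness, ethicality", and more. For the control arm it names only reasons for taking part and perceptions and experiences of the study.

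Statistical Analysis then commits to a comparison: "Adverse and serious adverse events will be summarised by arm, with risk differences and 95% confidence intervals but no hypothesis tests".

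**The concern.** A between-arm risk difference is interpretable only if events had the same chance of being found in each arm over the same period. Here the two arms share a T2 survey question, a T2 process questionnaire whose listed content differs by arm, and the freedom to contact the team. Thumos participants also have about five hours of therapist contact (two 120-minute workshops and a 60-minute call), and 20 of them are to be interviewed at T3. After T2, the only active contact named as an AE route is in Thumos.

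The AE definition covers any untoward medical occurrence, related or not, so events after T2 count as much as earlier ones. Safety Reporting promises all events in the final report and the published article. Readers will take a risk difference with an interval as a fair comparison. Omitting hypothesis tests does not change that, because the interval describes sampling error only.

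**Working it through.** The article states no AE rate or safety figure, so there is nothing to reproduce. The check has two parts: the share of follow-up that is covered, and the artefact that unequal detection would create.

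**Coverage.** Follow-up is 9 months from baseline: 9 × 365.25 / 12 / 7 = 39.1 weeks. With T2 at week 6, systematic enquiry covers 6 / 39.1 = 15%, leaving about 33 weeks (85%) to passive reporting. The Thumos date is tied to completion, so T2 may vary there. Weeks 4 and 8 give 10% and 20% covered.

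Under an assumed constant hazard with 9-month risk P, the risk by week 6 is 1 − (1 − P)^(6/39.1). For P = 10% this is 1.6%, so 84% of participants with a first event would have it after week 6. For P = 40% it is 7.5%, and the share is 81%.

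**Unequal detection.** Assume the same true risk p to T2 in both arms, survey capture s in both arms, and detection in Thumos only of a fraction e of the events that the survey misses.

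- Observed in the control arm: p × s
- Observed in Thumos: p × [s + (1 − s) × e]
- Spurious difference: p × (1 − s) × e
- 95% half-width with 110 per arm (220 randomised 1:1): 1.96 × √[(a(1 − a) + b(1 − b)) / 110], where a and b are the two observed risks

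All values of p, s and e are assumptions: p = 5, 10, 20%; s = 50, 70, 90%; e = 20, 50%. Selected results:

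| p | s | e | Thumos | Control | Spurious difference (points) | Half-width (points) |
|---|---|---|---|---|---|---|
| 5% | 90% | 20% | 4.6% | 4.5% | 0.1 | 5.5 |
| 10% | 70% | 50% | 8.5% | 7.0% | 1.5 | 7.1 |
| 20% | 90% | 50% | 19.0% | 18.0% | 1.0 | 10.3 |
| 20% | 50% | 50% | 15.0% | 10.0% | 5.0 | 8.7 |

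Over all 18 combinations the spurious excess runs from 0.1 to 5.0 points (apparent risk ratio 1.02 to 1.50) and the half-width from about 4 to 10 points. The excess is smaller than the half-width in every combination.

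**The case against.** The case against has several parts, and some of it stands.

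- **The T2 question is not the only channel shared by the arms.** A reader might infer that it is. Both arms are invited to complete the process questionnaire, its AE-related items are worded about the study rather than the intervention, the call-back applies to all participants, and anyone may contact the team. What remains is narrower: these items too are T2 only, and the article lists ethicality and affective attitude for Thumos alone.
- **Later events are not ignored.** A reader might say that most of follow-up is lost. Events raised at any point are followed up, so later ones are captured passively. Both arms also complete the PHQ-9, ReQoL-UI and sickness absence items at T3 and T4, so worsening mental health is measured alike in both. Those scales are not AE records, however, and do not feed the risk difference.
- **Non-completers are not shown to be missed.** Taken literally, the T2 timing in Trial design might suggest that a student who stops Thumos never receives the AE question, which would bias the difference downward. The documents do not support this. Table 3 allows an equivalent time, analysis is as randomised, and only the interviews exclude non-completers. The common timing simply needs stating.
- **Source and window may be set in the SAP.** The SAP and detailed protocol are not shown and could restrict the comparison. But the article itself fixes where AEs are asked about and which contacts feed in, and it commits to the risk difference without any restriction.
- **The size is hypothetical and the summaries are descriptive.** Both are true, and they limit the weight of the point.

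**Conclusion.** The point holds as an ascertainment problem in a descriptive safety comparison. As written, the plan asks both arms systematically only at T2, leaves about 33 of 39 weeks to passive reporting, adds detection routes in Thumos only, and then reports risk differences without a common source or window. Bias towards more events in Thumos is the most plausible direction. Its size cannot be derived from the article. The range of 0.1 to 5.0 points rests wholly on the assumed risk, capture and extra detection, on equal true risk, and on 110 per arm. It lies inside the sampling error of the comparison, but it is systematic and the interval gives no sign of it. The primary analysis is unaffected.

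**What to change.** 1. Add the same AE question to the T3 and T4 surveys in both arms for participants still in follow-up.
2. State that T2, with its AE question, goes to every randomised participant at a common time after baseline, whether or not Thumos was completed.
3. Base the between-arm AE risk difference on the common survey question, giving the number asked and the number responding by arm and time point.
4. Report all AEs and SAEs found by other routes in full, by arm and source, outside that risk difference, so that no known SAE is dropped.
5. Clarify whether both arms receive the same AE-related process-questionnaire items.

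The cost is one item in two existing online surveys, a minor amendment, SAP wording, slightly longer surveys and more AE follow-up contacts. Two limits remain. Recruitment began on 16 June 2025, so the first participants reached T3 around mid-October 2025 and T4 around mid-March 2026. T3 and T4 AE data will be missing for early recruits, and the report should say so. A survey-based comparison also depends on who responds, which is why response numbers by arm are needed. Steps 3 and 4 can be adopted at any time before analysis.
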